Transcranial direct current stimulation (tDCS) is a non-invasive method of brain stimulation that is capable of depolarizing or hyperpolarizing the neural membrane and as such, it has been used in people suffering from depression, by placing the anode (excitatory) over the left and the cathode (inhibitory) over the right DLPFC, or by placing the anode over the left DLPFC and the cathode over the right supra-orbital region.

For instance, in one study, 64 MDD patients were randomized to 15 sessions of 2 mA tDCS over 3 weeks, and tDCS was shown to be able to decreased MDD symptoms (20). However, in another study, not only active tDCS was superior to sham but also the combination of tDCS with sertraline was significantly more effective in reducing depressive symptoms than either treatment alone (21). Although tDCS *per se* showed promising results in treating MDD, the previous trial highlights that the effects of tDCS can be enhanced by combining it with other interventions. Overall, tDCS seems to decrease MDD symptoms by a pooled effect size of 0.36 (22). Moreover, according to a recent individual patient data meta-analysis, tDCS seems to be less effective in high-resistant patients, suggesting that tDCS may be a promising add-on therapy to therapies such as the cognitive behavioral therapy (CBT) (23) or cognitive control therapy (24, 25).

CBT is an empirically validated therapy for the treatment of MDD. Several studies have demonstrated the efficacy of CTB alone (26, 27) or as adjuvant to medication (28–30) in acute depression. Another advantage of CBT over anti-depressant drugs is its long-term effects, namely protecting against relapses and recurrences after active treatments has ended (27, 31, 32). Additionally, CBT is a well-established therapy that can restore or normalize abnormal brain activity, namely prefrontal alpha activity (33). Namely, an increase in left frontal brain activity after CBT in individuals with anxiety and depression.

It is important to highlight that MDD seems to induce profound changes in the brain, namely structural alterations in fronto-cingulate-striatal circuits (34–36). However, and somewhat surprisingly, first episode MDD patients have not been extensively studied with tDCS (37, 38). These first episode MDD patients provide an interesting opportunity, as their brains were not changed by the pharmacological treatments, by the time course, or by the recurrence of MDD episodes (and other comorbidities).

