### Eligibility Criteria

Participants will be included in this study if they meet the following criteria: 1) Aged 18–75 years; 2) Unipolar, nonpsychotic MDD (DSM-V); 3) Score in the MADRS 7 and above (mild, moderate, and severe depression); 4) Low risk of suicide, as evaluated during the clinical interview and through the Scale for Suicidal Ideation [Mild to Moderate SIS; (42)]; and 5) Able to sign informed consent.

Potential participants meeting any of the following criteria will be excluded: 1) any contraindication to receive tDCS (such as metal in the head, implanted brain medical devices); 2) any significant or unstable neurologic or psychiatric disorder other than MDD, such as epilepsy, Parkinson's Disease, Dementias, eating disorders, OCD Spectrum disorders, among others); 3) history of substance abuse within the past 6-months, 4) Any personality disorders; or 5) any severe life-threatening disorders or concurrent medical condition likely to worsen patient's functional status in next 6-months such as; cancer, or severe heart, kidney, or liver diseases. Participants with reported high risk of suicide will be excluded from the study and will be recommended to receive support from an experience and licensed psychologist/psychiatrist. Information about local and national institutions that provide support to cope with suicidal behaviors and though will be provided.

A screening questionnaire that addresses the specific inclusion and exclusion criteria will be applied to each participant prior to the SCID-5 interview and will help to screen out participants. Diagnosis will be performed using the Structured Clinical Interview for DSM-5 (SCID-5) (43, 44), a widely used semi structured clinical interview designed to evaluate psychopathology, following the categories in the DSM 5 (Diagnostic and Statistical Manual of Mental Disorders, Fifth Edition) for the clinical use and clinical research. Potential participants will also answer the tDCS eligibility questionnaire and the SIS to evaluate the likelihood of suicide attempt. Patients with high likelihood of suicide attempt will be not included in our study and will be recommend for psychological and/or psychiatric intervention.

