### Description of the Assessments

These instruments will be used at baseline, after the first 2 weeks of intervention, at the end of the 5-weeks of biweekly sessions and follow-up visits (up to 2 months after the intervention period) as detailed in the table below. Please see Table 1 for the complete assessments timetable.

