### Sample Size Calculation

For the sample size calculation, we assume an effect size(d) of 0.66 [upper limit for the 95% CI of the pooled effect size of tDCS on MDD (22) that for a two-side α of 0.05 and a power of 80%, requires a total of 76 patients (38 per group). We increased the sample size by 15% to 45 per group to account for unexpected factors. This sample size will be adequate to detect this magnitude of effect.

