### Statistical Analysis

#### Primary Outcome

A mixed model ANOVAs will be used to assess the clinical effects for primary outcome measure (MADRS), with intervention as between subject factor (active vs. sham tDCS), and time as within subject factor (weeks 2, 4, 8, 12, and 6 months). If there are significant baseline differences across the groups, those covariates will be included in the analysis (such as severity, anxiety, and quality of life). If significant main effects and/or interactions arise from the main analysis, *post-hoc* analysis corrected for multiple comparisons will be performed. If our hypothesis of prefrontal inter-hemispheric imbalance (as assessed by alpha power EEG) is confirmed, we will then conduct correlation analysis in order to assess whether these brain signatures correlate to long-term clinical effects in MDD.

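### Baseline covariates, including baseline severity, enter the primary MADRS model only if the arms differ significantly at baseline; this gives up precision and lets chance choose the model

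*Protocol article*

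**What the plan says.** The Statistical Analysis section of the protocol article, under Primary Outcome, sets the model: "A mixed model ANOVAs will be used to assess the clinical effects for primary outcome measure (MADRS"), with intervention as the between-subject factor and "time as within subject factor (weeks 2, 4, 8, 12, and 6 months"). Baseline is not among those levels.

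The next sentence gives the only covariate provision in the document: "If there are significant baseline differences across the groups, those covariates will be included in the analysis". Severity, anxiety and quality of life follow in brackets as examples. The list is open, and neither the baseline test nor its threshold is stated.

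Baseline MADRS will be available. Table 1 schedules it before the intervention, and Description of the Assessments says "These instruments will be used at baseline, after the first 2 weeks of intervention". Its spread should be wide, because Eligibility Criteria admits "Score in the MADRS 7 and above (mild, moderate, and severe depression").

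The Sample Size Calculation uses no covariate.

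**The concern.** Two things are at stake.

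**Precision.** Baseline MADRS is collected in every patient and plausibly predicts later MADRS. Adjusting for it narrows the confidence interval at almost no cost. Read literally, the protocol uses it only when a baseline test is significant. Allocation is random, so that test measures chance and not whether the variable predicts outcome.

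**Prespecification.** The form of the primary model is settled only after the baseline data have been examined, from an open list and with no stated threshold. Two analysts following the text could fit different models.

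This is a rule the protocol states, not a detail left to a statistical analysis plan. A plan that always adjusted for baseline MADRS would contradict the sentence.

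**Working it through.** **Inputs from the protocol.** Planning effect size: "we assume an effect size(d) of 0.66", two-sided α 0.05, power 80%, 38 per group raised to 45 (Sample Size Calculation). Pooled effect: "tDCS seems to decrease MDD symptoms by a pooled effect size of 0.36" (Background). Allocation 1:1 (Randomization).

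**Assumed, not in the documents.** Correlation r between baseline and follow-up MADRS of 0.3, 0.5 or 0.7; one follow-up comparison; normal data; a baseline test at the 0.05 level.

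**Step 1: the plan's own figure.** A two-sample t-test (noncentral t) with d = 0.66 has power 0.7998 at 37 per group and 0.810 at 38, so 38 reproduces. Inflation: 38/0.85 = 44.7, so 45. The stated sample size is an unadjusted one.

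**Step 2: how often the rule acts.** One test at 0.05 is significant in about 5% of randomised trials, so baseline MADRS is left out in about 95%. For three covariates the chance that at least one enters is 1 − 0.95³ = 0.143 if the tests are independent. It is about 0.13 at an assumed pairwise correlation of 0.5 and about 0.11 at 0.7.

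**Step 3: what unconditional adjustment gains.** Adjustment multiplies residual variance by 1 − r², so 45 per arm is worth 45/(1 − r²) unadjusted. Power uses the noncentral t with effect d/√(1 − r²) and 2 × 45 − 3 = 87 degrees of freedom.

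| | r = 0.3 | r = 0.5 | r = 0.7 |
|---|---|---|---|
| 1 − r² | 0.91 | 0.75 | 0.51 |
| Equivalent unadjusted n per arm | 49 | 60 | 88 |
| Power, d = 0.66, always adjusted (unadjusted 0.87) | 0.90 | 0.95 | 0.99 |
| Power, d = 0.36, always adjusted (unadjusted 0.39) | 0.42 | 0.50 | 0.66 |

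**Step 4: the conditional rule itself.** It was simulated for one covariate with 100,000 trials per scenario and 45 per arm: a baseline t-test, then ANCOVA if significant and the unadjusted t-test otherwise.

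| | r = 0.3 | r = 0.5 | r = 0.7 |
|---|---|---|---|
| SE of effect (SD units), conditional rule | 0.209 | 0.203 | 0.196 |
| SE, always adjusting (never adjusting 0.211) | 0.203 | 0.184 | 0.151 |
| Power at d = 0.66, conditional rule | 0.875 | 0.882 | 0.890 |
| Power at d = 0.36, conditional rule | 0.39 | 0.39 | 0.40 |
| Type I error, conditional rule | 0.048 | 0.043 | 0.035 |

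The rule recovers only a minority of the available precision and almost none of the power, and its test is slightly conservative.

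**Step 5: if baseline was meant as a time level.** The baseline-to-follow-up contrast has variance factor 2(1 − r) = 1.4/1.0/0.6, against 0.91/0.75/0.51 for ANCOVA. The difference, 2(1 − r) − (1 − r²) = (1 − r)², is never negative. At d = 0.36 the contrast has power 0.30/0.39/0.59, against 0.42/0.50/0.66 with ANCOVA.

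**The case against.** The strongest objection concerns the time list. It omits week 6, which the Abstract names for the primary outcome, and it does not match Table 1. In a list with those faults, the missing baseline level could also be a drafting slip, especially as the outcome is elsewhere described as improvement or reduction. This stands as a caveat: the model would then use baseline information through the group-by-time interaction, and the gain at r = 0.7 and d = 0.36 would run from 0.59 to 0.66 rather than from 0.39. It does not remove the point, because ANCOVA is still the more precise (Step 5).

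Second, the correlation is assumed, and the calculation uses one follow-up rather than the planned repeated-measures model. Both are true. The size is therefore a range, small at r = 0.3; the direction would not change.

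Four stronger readings are tempting, and the documents do not support them:

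- *A false-positive risk.* A reader might infer that data-dependent covariate choice inflates type I error. For a single covariate it does the reverse (0.035–0.048).
- *A biased estimate.* The unadjusted estimator is unbiased on average under randomisation. Only conditional on a realised imbalance in a prognostic variable is it off target.
- *An underpowered trial.* At the planning d = 0.66, unadjusted power is 0.87. Low power appears only at d = 0.36, and whether 0.66 was the right choice is a separate question.
- *A named covariate that is never measured.* Table 1 has no row labelled quality of life, but the text below it lists quality of life among the scales used at baseline. That is no part of this point.

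**Conclusion.** The point holds as one of precision and prespecification. The stated rule would leave baseline MADRS out of the primary model in about 95% of realisations. It would let chance add at least one of the three named covariates in about 11–14%.

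At r = 0.5, unconditional adjustment makes 45 per arm worth about 60. Compared with the unadjusted analysis, power rises from 0.87 to 0.95 at d = 0.66 and from 0.39 to 0.50 at d = 0.36. These sizes rest on the assumed correlation, a single follow-up comparison and the literal reading of the time levels. The validity of the test is not threatened. The change should be made because it costs almost nothing, and the article describes the trial as still recruiting.

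**What to change.** Replace the conditional sentence under Statistical Analysis, Primary Outcome. State that baseline MADRS, as a continuous covariate, is included in the primary model whatever the observed imbalance. Name in advance any further covariate to be used; none is required. Remove the significance test as a trigger for adjustment, and carry the same wording into the statistical analysis plan. While editing the paragraph, say explicitly whether baseline is a level of the time factor, so that it is not used both as an outcome level and as a covariate.

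Cost: a sentence or two of text, one degree of freedom per covariate, and no new data. The sample size need not change.

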## Research Question, Aims, Hypothesis

By combining two interventions that showed promising results in MDD (CBT and tDCS), we aim to investigate the clinical and underlying neurophysiological effects in first-episode drug naïve MDD patients. The main research question underlying this proposal is whether tDCS as add-on therapy to CBT in drug naïve, first-episode MDD patients could produce greater significant clinical improvements, as measured by the MADRS, when compared to CBT alone. We hypothesize that the combination of these therapies will produce a synergetic effect in the brain, potentiating the effects of CBT and decreasing the depressive symptomatology as assessed by the MADRS.

A secondary aim will be to perform the dose calculation (number of sessions) required to induce a clinically significant effect (50% decrease in the MADRS score). The underlying hypothesis is that the combination of tDCS with CBT will require a lesser number of sessions in order to elicit this clinical meaningful effect.

The second major scientific question is whether these clinical improvements will be correlated with the rebalancing of the inter-hemispheric asymmetry of EEG alpha activity toward the left hemisphere, as assessed by resting-state and emotional task eliciting-EEG. Here, the hypothesis is that both interventions (combined and alone) will reduce the inter-hemispheric alpha imbalance, as indexed by EEG power; however, that reduction will be more pronounced in the group that received the add-on intervention, as compared to CBT alone.

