**PRIMARY AND SECONDARY OUTCOME ASSESSMENTS**											
The satisfaction with life scale (SWL)		X			X			X		X	
The pittsburgh sleep quality index (PSQI)		X			X			X		X	
State-trait anxiety inventory (STAI-Y)		X			X			X		X	
Beck anxiety inventory (BAI)		X			X			X		X	
Beck's depression inventory (BDI)		X			X			X		X	
Montgomery-asberg depression rating scale (MADRS)		X			X			X		X	
Blinding questionnaire								X			
Visual analog scales (VAS)—pre and post				X			X				

Structured CBT sessions will follow the NICE guidelines from the National Institute for Health and Care Excellence (39). Patients will receive a total of 12 CBT sessions administered biweekly for 6 weeks. Mood, will be evaluated at the end of each week, as to perform the dose calculation (i.e., number of sessions) required to induce a clinical significant effect of at least 50% decrease in the MADRS scores.

In addition to the primary outcome measure (MADRS), secondary outcome measures will be clinical response as measured by scores on the 17-item Hamilton Depression Rating Scale, Beck Depression Inventory (BDI), Beck Anxiety Inventory (BAI), clinician-rated Clinical Global Impression–Severity of Illness scale, and quality of life (QoL). These scales will be used at baseline, week 2, 4, 6, and follow-ups (up to 6-month follow up).

Resting-state EGG assessments will be performed on baseline session, on weeks 2 and 6. These assessments will allow us to assess the neural effects of these interventions in the brain.

The Standard Protocol Items: recommendations for Interventional Trials (SPIRIT) statement were used as a framework for developing the study methodology for this trial (40, 41).

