#### Secondary Outcomes

Resting state EEG and task-elicited prefrontal EEG alpha asymmetry—Resting state EEG screening will be carried out before the intervention (baseline), and in the end of each week of intervention. Each screening will comprise a resting state EEG (3 min eyes open and 3 min eyes closed) and a task-related EEG data collection. The task-related screening will last about 3-min in an open-eyes active state. For this task, we will use a facial emotion task, with approach and avoidance facial expressions, similar to the task used by Stewart and colleagues

EEG will be acquired using 20 channel Starstim (Neuroelectrics, Barcelona, Spain), following the 10/20 system, in a continuous mode at a digitization rate of 500 Hz, with a bandpass filter of 0.01–100 Hz. Electrode impedances will be kept below 5 kΩ and EOG will be recorded from two additional bipolar channels. EEG data will be segmented into 1.5–3 s epochs centered on subject's responses (at least 50 epochs) using EEGlab.

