We also propose to study, as secondary aim, whether CBT combined with tDCS can engage the proposed mechanistic target, of restoring the prefrontal imbalance and connectivity, by changes over resting-state and task-eliciting EEG. This trial will help to evaluate the efficacy of this combined treatment as compared to CBT alone and to evaluate bilateral alpha activity over the prefrontal cortex. Thus, we also expect to demonstrate that these interventions are able to reduce the inter-hemispheric asymmetry of alpha EEG activity toward the left hemisphere reported in patients with depression. We expect that the combined intervention will induce greater asymmetry reduction (at least 50% minimum reduction). We also expect that this inter-hemispheric imbalance reduction will be correlated with mood improvement.

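### The EEG–MADRS correlation, the second major question, is planned only if an undefined imbalance hypothesis is confirmed, and only for long-term effects, so it may go unanswered or be reported selectively

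*Protocol article*

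**What the plan says.** **The question.** Research Question, Aims, Hypothesis states: "The second major scientific question is whether these clinical improvements will be correlated with the rebalancing of the inter-hemispheric asymmetry of EEG alpha activity". It sets no condition and no time point. The accompanying hypothesis is that "both interventions (combined and alone) will reduce the inter-hemispheric alpha imbalance", with a larger reduction in the active arm. The Discussion repeats the expected link with mood improvement, again without a condition.

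**The analysis.** The only correlation described is under Statistical Analysis, Primary Outcome: "If our hypothesis of prefrontal inter-hemispheric imbalance (as assessed by alpha power EEG) is confirmed, we will then conduct correlation analysis". Its stated aim is to assess "whether these brain signatures correlate to long-term clinical effects in MDD". The EEG Analysis subsection covers coherence, spectral power, artefact rejection and task-related power, and plans no correlation with MADRS.

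**The EEG visits.** Outcomes, Secondary Outcomes says: "Resting state EEG screening will be carried out before the intervention (baseline), and in the end of each week of intervention". The text after Table 1 says: "Resting-state EGG assessments will be performed on baseline session, on weeks 2 and 6". The EEG columns of Table 1 are pre-intervention, 15 days and post-intervention.

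**The concern.** The planned analysis is narrower than the question in two ways.

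1. **It is conditional.** A patient-level association between EEG change and symptom change can be estimated whether or not the group-level EEG result is significant, so the condition has no statistical purpose. If it is followed, the correlation appears only after a favourable EEG finding. Because the criterion is not defined, the decision to report can be made after the EEG data are seen.
2. **It concerns long-term effects.** Even when the condition is met, no stated analysis relates asymmetry change to MADRS improvement over the treatment period, where the article places its primary outcome.

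The article itself gives reason to expect that the condition could fail. The Background and the Discussion concede that some studies did not find the link between reduced left frontal activation and depression, and the Discussion gives this as a reason for choosing this population. A null group result would be informative here, and that is when the correlation would be dropped.

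**Working it through.** **Step 1. Text against text.**

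| | Question (Research Question; Discussion) | Planned analysis (Statistical Analysis, Primary Outcome) |
|---|---|---|
| Condition | None | Imbalance hypothesis confirmed, criterion not given |
| EEG side | Rebalancing of alpha asymmetry | Brain signatures |
| Clinical side | Clinical improvement; mood improvement | Long-term clinical effects |

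This mismatch needs no assumption about effect size.

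**Step 2. What confirmation could mean.** The article allows at least four readings: imbalance present at baseline, reduction within the arms, greater reduction in the active arm (Research Question), or a reduction of at least 50% (Discussion).

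**Step 3. The plan's own figure.** No figure is given for the EEG condition or the correlation, so the check starts from Sample Size Calculation (d = 0.66, two-sided 0.05, 80% power). A two-sample t-test needs 37.02 per arm, rounded up to 38, or 76 in total as stated. Allowing for 15%: 38 / 0.85 = 44.7, rounded up to 45 per arm as stated.

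**Step 4. Chance that the correlation is not run.** The article gives no EEG effect size. The values 0.36 (Background) and 0.66 (Sample Size Calculation) are its figures for symptoms, borrowed here as assumptions for EEG. The values 0.20 and 0.50 are further assumptions. The chance is 1 − power of a two-sided 5% t-test, with these noncentrality parameters:

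- between arms, 45 per arm: d × √(45/2)
- within patients, one arm: d × √45
- within patients, both arms pooled: d × √90

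For example, between arms at d = 0.36: 0.36 × 4.743 = 1.71, power 0.393, not run 0.607.

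| Assumed d | Between arms, 45 per arm | Within one arm, n = 45 | Within patients, pooled n = 90 |
|---|---|---|---|
| 0.20 | 84% | 74% | 53% |
| 0.36 | 61% | 34% | 8% |
| 0.50 | 35% | 9% | under 1% |
| 0.66 | 13% | 1% | under 1% |

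The within-patient d is in units of the SD of change, so values in one row are not the same biological effect. The table shows only how far the answer depends on the criterion.

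**Step 5. Is the unconditional analysis feasible?** By Fisher's z, the smallest correlation detectable with 80% power at two-sided 0.05 is tanh((1.960 + 0.842)/√(N − 3)). With N = 90 this is tanh(2.802/9.327) = 0.29. With N = 76 it is 0.32. For an assumed r of 0.30, power is 82% with 90 patients and 75% with 76. The article gives no expected r, and a regression adjusted for arm and baseline will differ somewhat from this approximation.

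**The case against.** The strongest reply is that the article does not say *only*. It also gives EEG a prognostic role, so the long-term correlation could be that prognostic analysis. The end-of-treatment correlation would then simply be left to an analysis plan that is not shown. This is a fair reading of the long-term wording and softens that half of the point. It does not remove the condition, which is a stated rule on the only correlation described and not an omitted detail.

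Four stronger readings are tempting, and the article does not support them:

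- **That the question will often go unanswered.** Step 4 shows that this depends on a criterion and an EEG effect that the article does not give.
- **That the whole mechanistic aim goes unreported.** Nothing makes the power, task-related power or coherence analyses conditional. The group asymmetry hypothesis can still be tested and a negative result reported. Only the correlation depends on it.
- **That the hypothesis is about week 6.** The Research Question section names no visit. Week 6 comes from the Abstract, and Trial Design places the primary outcome at week 2.
- **That pooling the arms would create a spurious correlation.** The article does not say that the arms will be pooled.

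It would also be wrong to answer by demoting coherence to exploratory status. Connectivity is part of the secondary aim in the Abstract and the Discussion.

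The conflict over EEG visits is real but separate. It matters here because it determines which EEG change can enter the correlation, and it adds nothing to the case against the condition.

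**Conclusion.** The point holds in limited form. A question ranked second in the trial is posed without condition, but its only described analysis depends on an undefined confirmation and concerns long-term effects. It may go unanswered or be reported selectively, and no correlation with on-treatment or end-of-treatment MADRS improvement is stated.

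The textual mismatch rests on no assumption. The size of the risk cannot be fixed: under 1% to 84% over assumed EEG effects of d = 0.20 to 0.66 and three possible significance criteria. A reader might take the 61% between-arm figure at d = 0.36 as the expected failure rate. That would require both the between-arm criterion and the transfer of a symptom effect to EEG, and the article supports neither.

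The consequence is confined to a secondary mechanistic analysis. The primary MADRS comparison is not affected. The change is worth making because it is cheap, and the article reports that the trial is still recruiting.

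**What to change.** - **Remove the condition** in Statistical Analysis, Primary Outcome. Regress MADRS at the primary time point on change in frontal alpha asymmetry from baseline to the same visit, adjusted for baseline MADRS and arm. Report the coefficient with its 95% CI whatever the group EEG result.
- **Settle the time point.** The Abstract says week 6 and Trial Design says week 2. These must be reconciled, and the regression should use the resulting visit. EEG is scheduled at both weeks.
- **Keep the long-term correlation** as an additional analysis. If any condition is retained for it, state the test, contrast, visit and threshold in advance.
- **Reconcile the EEG schedule** in Outcomes, Secondary Outcomes (end of each week) with the text after Table 1 and the table's EEG columns (baseline, weeks 2 and 6).
- **Leave coherence** in its present role.

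The cost is a change of wording and one regression. The downside is one more secondary result to report, possibly null. If EEG visits follow Table 1, no additional data collection is needed.
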